#### Uremic toxin measurement

Serum samples of indoxyl and p-cresol sulphate will be collected by the start and end of each treatment period. The concentrations of free and total p-cresol sulphate and indoxyl sulphate will be measured by high-pressure liquid chromatography [21]. Total p-cresol sulphate and indoxyl sulphate will be measured after deproteinization of serum with ethanol. These analyses will be conducted at McMaster University in Hamilton, ON.

#### Gut microbiome

Two faecal samples will be collected from consecutive days for analysis at the end of the run-in and each treatment period. Participants will collect the faecal sample; they will be provided collection kits and an ice pack and instructed to collect a single sample from 3 separate places on the stool using a spoon attached to the cap of the collection tube. Participants will be instructed to store the collected faecal samples in their household − 20 °C freezer with the provided ice pack, until transport back to the study centre. At the study centre, samples will be aliquoted and then stored at − 80 °C. Faecal samples will undergo genomic DNA extraction following the manufacturer’s protocol. Experimental negative controls will be included in extraction protocols to confirm the reliability and consistency of the extracted nucleic acid. The V4 hypervariable region of 16S rRNA gene will be amplified; the sequencing library will be generated and sequenced by Microbiome Insights (www.microbiomeinsights.com) in Vancouver, BC.

#### Anthropometry

Body weight and waist circumference will be measured at the beginning and end of each period.

#### Edmonton Symptom Assessment Scale (ESAS)

ESAS will be completed at the beginning and end of each period through paper or online by REDCap. The ESAS is a widely used tool for measuring physical and psychological symptom distress that has been validated in individuals with CKD [22], which consists of nine visual analogue scales (0–10 scale) for pain, activity, nausea, depression, anxiety, drowsiness, appetite, well-being, and shortness of breath. The scale for each symptom is anchored by the words “no” and “severe” at 0 and 10, respectively.

#### Quality of life

The Medical Outcomes Study Short Form 36-item Questionnaire (SF-36) will be used to measure the quality of life and has been validated in individuals with CKD [23]. SF-36 will be filled in by the beginning and end of each period. The questionnaire is designed for use across diverse populations and healthcare settings and is composed of eight scales: physical functioning (PF), role functioning/physical (RP), bodily pain (BP), general health (GH), vitality (VT), social functioning (SF), role functioning/emotional (RE), and mental health (MH). These scales are scored from 0 to 100, with higher scores indicating better function.

#### Dietary intakes and nutritional assessment

Participants will complete three dietary recall surveys (for two weekdays and one weekend) following the run-in, and in the last week of each treatment period, using the Automated Self-Administered 24-h Canada (ASA24®) dietary assessment tool. The ASA-24 is a web-based tool that enables multiple, automatically coded, self-administered 24-h recalls. Participants will receive training and have support from study staff in filling out the recalls.

#### Clinical chemistry

Blood and urine samples for clinical chemistry will be collected at the start and end of each treatment period. In the blood, albumin, BUN, bicarbonate, calcium, chloride, creatinine, eGFR, glucose, phosphorus, potassium, sodium, and HbA1c will be measured. In the urine, albumin, albumin/creatinine ratio, glucose, and total protein will be measured. All samples will be collected, and analytes will be measured by Shared Health Diagnostics at Seven Oaks Hospital.

#### Metabolomics

Serum, faecal, and urine samples will be collected at the end of run-in and treatment periods. The metabolomics analyses and informatics will be conducted by McMaster University in Hamilton, ON. Targeted analysis of water-soluble metabolite classes including amino acids, sugars, alcohols, organic acids, amines, TCA cycle intermediates, and short-chain fatty acids using quantitative NMR spectroscopy will be conducted on serum collected at the endpoint of each study period [24]. A targeted quantitative metabolomics approach will be used to analyse urine samples using a direct injection mass spectrometry with a reverse-phase LC-MS/MS assay. Serum and urine samples will be collected in accordance with metabolomic sample collection guidelines, allowing as much as possible that the original metabolic profile of the fresh samples is maintained and minimizing potential pre-analysis sample collection or handling issues that could bias the results of the metabolomic analyses [25].

### Sample handling

Blood and urine samples will be collected by the certified phlebotomist in Shared Health Diagnostics at Seven Oaks Hospital. The laboratory will process and run the analysis for the clinical chemistry and store the serum and urine sample in − 80 °C freezer in the Shared Health lab for uremic toxic measurement and metabolomics analysis. The blood and urine samples will be collected by the start and end of each treatment phase. For stool samples, participants will be provided collection kits and an ice pack and instructed to collect a single sample from 3 separate places on the stool using a spoon attached to the cap of the collection tube. Participants will be instructed to store the collected faecal samples in their household − 20 °C freezer with the provided ice pack, until transport back to the study centre. At the study centre, samples will be aliquoted and then stored at − 80 °C in the Shared Health Diagnostics Lab. These samples may be moved to storage located at the University of Manitoba if required due to space constraints. Faecal samples will be collected at the beginning and end of treatment periods 1 and 2. At least one sample will be obtained during those two consecutive days if possible. Samples will be sent out for blood, faecal, and urine metabolomics analysis and gut microbiome analysis, following shipping guidelines of the contracted service providers, University of Manitoba policies, and all applicable local and national regulations.

### Qualified investigator responsibilities

The qualified investigator (QI) will be responsible for determining the eligibility of individuals to participate in the trial. Although some tasks may be delegated to other qualified clinical trial staff members, the QI will ensure the individual or party is qualified to perform those study tasks and is responsible for supervising any individual or party to whom tasks are delegated at the trial site. The QI assumes ultimate responsibility for the overall conduct of a clinical trial and for compliance with all applicable regulations and guidelines. The QI must document the delegation of tasks/duties. The QI will evaluate the general health and review the participants’ medical history, vital sign results, concomitant medications, and all laboratory results to determine the eligibility for the trial. The QI will have ongoing responsibilities of monitoring adverse events, serious adverse events, concomitant medications, and any additional laboratory results to ensure participant safety through the entire clinical trial. All study-related medical decisions are made, unless delegated to a qualified and trained sub-investigator by the QI. The QI is ultimately responsible for the welfare and safety of all participants on the trial. The QI agrees that the site will permit, if required, study-related monitoring, audits, REB review, and regulatory inspection(s), providing direct access to source data/documents. It is the responsibility of the QI or designee to maintain adequate clinical study records. Copies of all clinical study material must be archived for a period defined by Canadian regulations. It is also the responsibility of the QI to ensure that the study is conducted in accordance with the principles of Good Clinical Practice and according to the applicable local laws and regulations concerning studies conducted on human participants which are outside the definition of a medical product or medical device. The QI will have access to all product codes and may break randomization codes if necessary, for handling an adverse event. Lastly, the QI or their designee will review the deviations and determine if the deviation(s) would significantly affect the results and, if deemed necessary, not include such data in statistical analysis. The QI will ensure that all study documents are maintained up to date as specified in the Essential Documents for the Conduct of a Clinical Study and as required by the applicable regulatory requirements. The QI will ensure that all serious adverse events are immediately reported to Health Canada, the University of Manitoba REB, and any other applicable regulatory authorities.

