### Randomization, blinding, and code-breaking

Eligible patients (*n* = 36) will go through assessments at baseline and will be randomly allocated to 2 groups, each consisting of 18 participants. Randomization will be done by an independent researcher in the biostatistics platform at the George and Fay Yee Centre for Healthcare Innovation (CHI) at the University of Manitoba. Randomization will be performed using code written in the R statistical programming language (version 3.5.3). Treatments will be assigned with a 1:1 ratio. A total of 48 randomization cards will be prepared, one set of 24 for each sex. The randomization schedule will be transferred into sets of opaque sealed envelopes. After a participant’s baseline visit, the study staff will open a sealed envelope which will contain the participant’s allocation. The order of the interventions will be blinded for both the investigators and the participants. Treatments will be given in sealed sachets; sachet content will be blinded by an outside party, given to the study staff labelled as A or B, and dispensed to participants according to their treatment period. Treatments will not be unblinded until the analyses are complete, unless required due to adverse events during the clinical trial. There will also be a midpoint review of the participants’ clinical data by an independent nephrologist who will be unblinded (see the “Qualified investigator responsibilities” section).

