#### Inclusion in analysis

The primary analysis will be conducted using the All Participants (intent-to-treat) analysis set. The primary analysis will be repeated in the *Completers* analysis set. Demographics and all other baseline measurements will be analysed in the All Participants set as well as in the Completers set.

Completers analysis set: all participants who have completed the trial

All Participants analysis set: all randomized participants

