### Discontinuation/withdrawal of participants from trial treatment

Each participant has the right to withdraw from the trial at any time. Participants may discontinue trial participation at any time and are requested to contact a research team member to inform them of their decision. In addition, the investigators may discontinue a participant from the trial at any time if the investigators consider it necessary for any reason including pregnancy, ineligibility (either arising during the trial or retrospectively having been overlooked at screening), significant protocol deviation, significant non-compliance with the protocol, disease progression which results in the inability to continue to comply with the protocol, withdrawal of consent, and loss to follow-up.

Withdrawal will not result in the exclusion of the data for that participant from the analysis. As the primary analysis will be based on an intention-to-treat, there will also be a completer only analysis performed.

If a participant is withdrawn within the first 4 weeks of the trial, they will be replaced. If the replacement participant is withdrawn, there will be no subsequent replacement.

The reason for withdrawal will be recorded in the CRF, if provided.

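### The discretionary rule for dropping data after protocol deviations is not confined to sensitivity analyses and conflicts with the primary analysis of all randomized participants

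*Protocol article*

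**What the plan says.** Five parts of the protocol article bear on whose data enter the primary analysis.

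- **Qualified investigator responsibilities.** The QI or a designee reviews deviations and is to "determine if the deviation(s) would significantly affect the results and, if deemed necessary, not include such data in statistical analysis". The sentence does not say which analysis it means. Shortly before it, the same section states: "The QI will have access to all product codes and may break randomization codes if necessary, for handling an adverse event".
- **Inclusion in analysis.** "The primary analysis will be conducted using the All Participants (intent-to-treat) analysis set". The set is defined without exceptions: "All Participants analysis set: all randomized participants". The only other set is Completers.
- **Discontinuation/withdrawal of participants from trial treatment.** A significant protocol deviation is one of the listed reasons for which investigators may discontinue a participant. The section adds: "Withdrawal will not result in the exclusion of the data for that participant from the analysis".
- **Procedure for accounting for missing, unused, and spurious data.** Unusual records that cannot be explained may be left out when an analysis is repeated, and the repeats are presented as sensitivity analyses.
- **Randomization, blinding, and code-breaking.** "The order of the interventions will be blinded for both the investigators and the participants". Also: "Treatments will not be unblinded until the analyses are complete, unless required due to adverse events during the clinical trial".

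**The concern.** An intent-to-treat primary analysis fixes its population at randomization. A rule that lets someone at the site decide later that data tied to a deviation are not analysed undoes this, unless the rule is confined to a secondary analysis. Here it is not, and the article does not say which rule prevails.

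The criterion adds to the difficulty. It can be read in two ways: as a test of how serious a deviation is, made without looking at outcomes, or as a test of what the deviation does to the trial's result. Under the second reading, exclusion would depend on the outcome.

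What is at stake is the primary treatment comparison. In a crossover with about 30 completers, each participant carries considerable weight, so a few discretionary exclusions in one direction can move the estimate and its p-value.

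**Working it through.** **1. The rules side by side**

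Take a randomized participant with a significant protocol deviation whose serum samples were collected.

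| Section | Consequence for the primary analysis |
|---|---|
| Inclusion in analysis | Data are in, because the participant was randomized |
| Discontinuation/withdrawal | If withdrawn for the deviation, data stay in |
| Qualified investigator responsibilities | Data may be left out, at the discretion of the QI or a designee |
| Missing, unused, and spurious data | Unusual records are left out only in sensitivity analyses |

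The third row cannot be squared with the first. It also produces an odd result beside the second: a participant withdrawn because of a deviation keeps their data in the analysis, while one who deviates and remains in the trial can lose theirs. The fourth row shows that the plan elsewhere confines a similar exclusion to sensitivity analyses. The section on reporting deviations only has them tabulated and listed, so it does not settle the conflict.

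**2. The plan's own figure**

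Inputs from Sample size calculation: SD 45 μmol/L, within-person correlation 0.79, difference 17.5 μmol/L, 30 participants, two-sided alpha 0.05, stated power 0.88.

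- SD of the within-person difference = 45 × √(2 × (1 − 0.79)) = 29.16 μmol/L.
- Standard error at n = 30 = 29.16 / √30 = 5.32 μmol/L.
- Power from the noncentral t distribution: 0.888 with 29 degrees of freedom, 0.887 with 28. The stated 0.88 is reproduced.
- Smallest observed difference reaching p < 0.05 with 28 degrees of freedom = 2.048 × 5.32 = 10.9 μmol/L.

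**3. Illustration under assumed numbers**

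The article gives no deviation rate and no expected number of exclusions, so everything in this step is assumed. Each participant contributes one difference, RPS minus cornstarch, and period effects are ignored.

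- *Extreme case.* Two of 30 participants are dropped, each 60 μmol/L to the unfavourable side of the mean (60 / 29.16 = 2.06 SD). The shift is 2 × 60 / 28 = 4.3 μmol/L towards RPS. That is 4.3 / 5.32 = 0.8 standard errors, or 4.3 / 17.5 = about a quarter of the target difference.
- *Less extreme cases.* These were simulated with no true effect, n = 30, deviators a random subset, and the least favourable deviators dropped by someone who knows allocation and outcome:

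| Dropped | Shift towards RPS (μmol/L) | False-positive rate favouring RPS (nominal 0.025) | Two-sided rate (nominal 0.05) |
|---|---|---|---|
| 1 of 3 deviators | 0.8 | 0.035 | 0.052 |
| 2 of 6 deviators | 2.0 | 0.054 | 0.063 |
| 3 of 9 deviators | 3.2 | 0.084 | 0.090 |

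- *Exclusions unrelated to outcome.* These cause no such bias but still cost power: 0.887 at n = 30, 0.863 at n = 28, 0.850 at n = 27.

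**The case against.** **The review may well be blinded.** A reader might infer that the QI, having access to product codes, selects data unblinded, and that the claim of investigator blinding therefore fails. The article does not support that. The limitation to handling an adverse event may govern the access to codes as well as the breaking of them. The randomization section calls investigators blinded and allows unblinding before the analyses are complete only for adverse events. Nothing says deviations are reviewed with knowledge of treatment. What remains is that the exclusion clause does not itself require a blind reviewer.

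**The criterion may be a test of seriousness.** The wording is conditional, and what is judged is the deviation, for example a mistimed sample. A reader might take it as established that exclusion depends on the observed result, but the text permits either reading. The objection stands to that extent. It does not remove the conflict, because exclusion by discretion after randomization is incompatible with the primary set under both readings.

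**The contradiction has limits.** The analysis-set definition concerns participants, while the clause concerns data tied to a deviation, and the withdrawal section is about withdrawal rather than deviations as such. In addition, the missing-data section already excludes participants with missing values for a required variable, so any departure from intent-to-treat cannot be charged to this clause alone. All of this is fair. But in a crossover with few measurements per participant, removing data can amount to removing the participant, and the missing-data rule turns on missingness, not on someone's judgement.

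**The 4.3 μmol/L is an extreme.** Under normality, a value 2.06 SD to one side has probability 0.020, so about 0.6 such participants are expected among 30. The chance of at least two is 0.6% among 6 deviators and 1.3% among 9. This stands, and the figure is not a forecast.

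**Detail may sit in the SAP, and the trial is called exploratory.** Deviation categories and timing are commonly left to the SAP, and their absence from the article is not held against it. The point rests on a rule that the article does state. The exploratory label does not dispose of it, since the Discussion says the results will form the basis of a larger multicentre trial.

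**Conclusion.** The conflict holds. One section gives the QI or a designee discretion to leave data out of the statistical analysis because of a deviation, without confining this to a sensitivity analysis. Another fixes the primary analysis on all randomized participants, and a third keeps data after withdrawal for reasons that include such deviations. The primary analysis is therefore open to selective exclusion. This conclusion is textual and does not depend on any calculation or on the QI being unblinded.

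Two stronger statements are not established: that deviations are reviewed with knowledge of treatment, and that exclusion is decided on the observed results.

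The size is unknown, because the article gives no deviation rate. Under the assumed scenarios the shift runs from 0.8 to 4.3 μmol/L, against a standard error of 5.3 and a target difference of 17.5 μmol/L. All of these scenarios assume that the dropped participants lie on the unfavourable side. The upper end needs two participants each about 2 SD out.

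**What to change.** Amend the exclusion sentence under Qualified investigator responsibilities so that:

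- deviations are reviewed, classified and listed, but do not remove collected data from the All Participants primary analysis;
- any exclusion because of a deviation appears only in a labelled sensitivity analysis, in line with the handling of unusual records;
- those exclusions are decided before unblinding, by people without access to the codes.

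It would also help to make clear whether the limitation to adverse-event handling covers the QI's access to product codes as well as code-breaking.

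The cost is a change of wording in the protocol, carried into the SAP. The downside is that some deviating records stay in the primary analysis, where they may add noise or dilute a true effect. The sensitivity analysis would show how much they matter.

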
### Safety monitoring committee

The interventions in this trial are low risk, and they are in addition to standard care that the participants will continue to receive throughout the trial period and after the trial is completed; therefore, no data and safety monitoring board (DSMB) will be formed. However, there will be an external review of the participant clinical chemistry and any trial AEs at the trial midpoint when all participants have completed their first treatment period. This review will be conducted by a nephrologist from outside of Manitoba. This review will monitor evidence for treatment harm, looking for trends in the clinical chemistry and/or increases in un/expected events, related to the treatments and take appropriate action. These actions may include proposing protocol changes they could include early stopping of the trial due to clear harm of a treatment depending on the results of the review.

### Statistical analysis

The bioinformatics and statistical analyses of microbiome data will be performed with the assistance of Microbiome Insights and the Data Science platform at CHI; it will be updated based on the recommendations and technology advancements between now and the processing of the samples. In general, the default settings of the FLASH assembler [22] will be used to merge the overlapping paired-end Illumina fastq files. UPARSE algorithm [23] will be used for (a) quality filtering of the reads based on the maximum expected error value = 1.0, (b) identification of unique sequences, (c) abundance sorting and removal of singletons, (d) clustering the reads into operational taxonomic units (OTUs) based on 97% identity threshold, (e) de novo and reference-based chimera checking (against GOLD database [22]), and (f) construction of OTU table. Taxonomic classification will be then carried out using QIIME [26] implementation of UCLUST [24] and will be aligned against the Greengenes database using the PyNAST algorithm [25]. Phylogenetic trees were built with FastTree [27] for further comparison between microbial communities. Prior to performing downstream analyses, the resulting OTU table will be filtered to remove all the samples with low-sequencing depths. Community richness and diversity indices will be then calculated using QIIME at a given even depth per sample. Phylogenetic- (weighted UniFrac distances) and abundance-based (Bray-Curtis dissimilarity) β-diversity metrics will be calculated following normalization of the final OTU table using the cumulative sum scaling (CSS) transformation [28]. Principal coordinate analysis (PCoA) will be applied on the resulting distance matrices to generate two-dimensional plots using default settings of the PRIMER-6 software (PRIMER-E Ltd, Plymouth). Unsupervised clustering analysis will be performed to relate clustering patterns of samples to the proportion of the core OTUs within each niche (core OTUs defined as those present in at least 75% of samples in each niche). The relative abundances of the selected OTUs will be normalized across samples. Bray-Curtis dissimilarities will be calculated using the R “vegan” package [29], and the resulting matrix will be subjected to unsupervised hierarchical clustering using the R “dendextend” package [30] and will be visualized over the heatmap of abundance matrix using the R “complexheatmap” package [31]. The UNIVARIATE procedure of SAS will be used for testing the normality of residuals for α-diversity measurements. Non-normally distributed data will be either log or Box-Cox power transformed and then subjected to analysis of variance (ANOVA) test using MIXED procedure of SAS. All pairwise comparisons among the groups will be tested using Tukey studentized range adjustment. Permutational multivariate analysis of variance (PERMANOVA; implemented in the Primer6 software) will be used to detect significant differences between β-diversity metrics of microbial communities. The relative abundances of selected core OTUs will be tested for statistically significant associations with available metadata using multivariate analysis with linear modelling (MaAsLin) [32] accounting for all potential confounders (covariates) that could be associated with the profile of microbiome (i.e. sex, age, BMI) and participants (treated as a random factor). Significant associations will be considered below a *q*-value threshold of 0.1. To assess the shifts in functionality of microbiome, correlation network analysis (CoNet, [33]) will be used to explore microbial co-occurrence/mutual-exclusion relationships and identify hub OTUs that show the highest number of positive/negative correlations with other OTUs under treatment conditions.

Effects of treatment on linear outcomes at the end of each period will be analysed by the SAS MIXED (SAS 9.4) procedure. Sequence and sex will be included in the model as fixed factors, and participants will be included as a repeated factor. The normality of the data distribution will be done using the Shapiro-Wilk test, and the non-normal variables will be transformed prior to analysis. Demographic data will be reported as the mean ± standard deviation. The results will be reported as least-squared means ± standard error of the mean (SEM) unless otherwise specified. Statistical significance will be set at *p* < 0.05 for all analyses. The Data Science Platform in CHI will provide data management support in addition to biostatistics support for the project.

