**Methods:**

This is a double-blind, randomized two-period crossover trial. Thirty-six eligible participants will consent to follow a 26-week study regimen. Participants will receive 2 sachets per day containing either 15 g of RPS (MSPrebiotic, resistant potato starch treatment) or 15 g cornstarch (Amioca TF, digestible starch control). Changes in blood uremic toxins will be investigated as the primary outcome. Secondary outcomes include the effect of RPS consumption on symptoms, quality of life and abundance, and diversity and functionality of the gut microbiome.

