### Outcome measures

Serum concentrations of indoxyl and p-cresol sulphate are considered the primary outcome of this trial. This is to investigate how RPS consumption influences blood uremic toxins. The abundance, diversity, and functionality of the gut microbiome will be investigated as the secondary outcomes. Samples will be sent out for blood, faecal, and urine metabolomics analysis and gut microbiome analysis, following shipping guidelines of the contracted service providers, University of Manitoba policies, and all applicable local and national regulations.

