### Sample size calculation

A final samples size of 30 participants in this study will be able to detect a difference between the treatments in total p-cresol sulphate of 17.5 μmol/L, or ~ 15% change, at a power of .88 (alpha = 0.05, two-sided), given a within-person correlation of .79 [23] and an estimated standard deviation of 45 μmol/L [9] for total p-cresol sulphate. A 30% or greater drop in uremic solutes would be considered clinically significant, warranting additional trials investigating this prebiotic intervention in CKD, and we are confident we would be able to detect such a change should it occur. To account for the loss of power due to dropouts, we will recruit 36 participants.

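### The abstract makes changes in uremic toxins primary, but the analysis and the stated power fit end-of-period concentrations; define the variable once and consider using the start-of-period samples already drawn

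*Protocol article*

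**What the plan says.** The primary variable is described in three places in the protocol article.

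- Abstract, Methods: "Changes in blood uremic toxins will be investigated as the primary outcome".
- Outcome measures: "Serum concentrations of indoxyl and p-cresol sulphate are considered the primary outcome of this trial". No time point or change is named.
- Statistical analysis: "Effects of treatment on linear outcomes at the end of each period will be analysed by the SAS MIXED (SAS 9.4) procedure".

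On sampling, Uremic toxin measurement says: "Serum samples of indoxyl and p-cresol sulphate will be collected by the start and end of each treatment period". Table 1 places the blood collections at days 15, 84, 113 and 182, so each participant gives four values. Both start-of-period samples (days 15 and 113) follow a stretch on cornstarch, the run-in and the washout.

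On the model, the statistical section says: "Sequence and sex will be included in the model as fixed factors", with participants as the repeated factor. It mentions no start-of-period value.

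On power, Sample size calculation starts from "A final samples size of 30 participants in this study", able to "detect a difference between the treatments in total p-cresol sulphate of 17.5" μmol/L with power 0.88 at two-sided alpha 0.05. The SD is 45 μmol/L, "given a within-person correlation of .79". It does not say which pair of samples that correlation describes.

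**The concern.** A change from period start and an end-of-period value are different analysis variables. In a crossover, a comparison of changes combines four measurements per person and a comparison of end values combines two, so their precision can differ a good deal. The article gives one power figure and does not tie it to either variable by name. If the abstract were taken literally, that figure might not apply, and the choice between the two could be made after seeing data.

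A second, smaller matter is that the start-of-period toxins are measured anyway. If samples within a period are more alike than samples from different periods, those values could sharpen the treatment comparison, but the described model gives them no role.

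**Working it through.** **Inputs** (Sample size calculation): n = 30, difference 17.5 μmol/L, SD 45 μmol/L, within-person correlation 0.79, two-sided alpha 0.05. Visit days come from Table 1. Power is from the noncentral t distribution, with 28 df for unadjusted comparisons (two sequences) and 27 df with a baseline covariate.

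**Notation.** r_b is the correlation between samples from different periods. r_w is the start-to-end correlation within a period. The protocol gives a single value, 0.79; r_w is not given separately and is varied below as an assumption.

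**1. The plan's own figure (one end value per period).**
SD of difference = 45 × √(2 × (1 − 0.79)) = 45 × √0.42 = 29.2.
Power = 0.887 (0.888 with 29 df). The stated 0.88 is reproduced.

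**2. Change from period start.** For (E1 − B1) − (E2 − B2), with all cross-period correlations equal, the variance is 4 × SD² × (1 − r_w).
With r_w = 0.79: SD = 45 × √(4 × 0.21) = 45 × √0.84 = 41.2, and power is 0.61. It is 0.70 if all 36 recruited participants are evaluable, and about 57 evaluable participants would be needed for 0.88.

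The two variances are equal when 4(1 − r_w) = 2(1 − 0.79), that is, r_w = 0.895.

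**3. End value adjusted for the start-of-period difference.** The residual variance is SD² × [2(1 − r_b) − (2(r_w − r_b))² / (2(1 − r_b))].
At r_w = 0.85: 0.42 − 0.12²/0.42 = 0.3857, and SD = 45 × √0.3857 = 27.9.

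**4. Time-decay scenario (assumption).** Correlation falls exponentially with time and equals 0.79 at the 98 days between the two end visits. Start and end of a period are 69 days apart, so r_w = 0.79^(69/98) = 0.847. The other pairs follow in the same way.

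| Scenario (end-to-end correlation 0.79) | Change: SD, power | Adjusted end value: SD, power |
|---|---|---|
| All pairs 0.79 | 41.2, 0.61 | 29.2, 0.886 |
| Time decay | 36.4, 0.72 | 28.4, 0.90 |
| r_w = 0.85, others 0.79 | 34.9, 0.76 | 27.9, 0.91 |
| r_w = 0.90, others 0.79 | 28.5, 0.90 | 24.8, 0.96 |

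The unadjusted end value has SD 29.2 and power 0.887 in every row.

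**5. Why the covariate should be split.** The best within-person slope is (r_w − r_b)/(1 − r_b): 0 when all pairs are 0.79, and 0.06/0.21 = 0.29 at r_w = 0.85. The between-person slope is (r_w + r_b)/(1 + r_b), which is 1.58/1.79 = 0.88 when all pairs are 0.79. A single unsplit covariate forces one slope on both.

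**The case against.** Three points favour the plan as written.

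First, the operative sections agree. Outcome measures, Statistical analysis and Sample size calculation all fit an end-of-period concentration, and 0.88 is right for it. Only the abstract says otherwise. Sample size calculation itself uses the word change for the contrast between treatments, so the abstract may mean no more than that. This stands. A reader might infer that the stated power is wrong or that the trial is underpowered, and the documents do not support that.

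Second, the change-score shortfall depends on a correlation that the protocol does not report. At a start-to-end correlation of 0.90 the power would be 0.90. The shortfall also concerns the 15% difference. The protocol's clinically significant drop is 30%, about 35 μmol/L (17.5/0.15 × 0.30), and even the least favourable change-score case above has power 0.994 for that. This stands too, in a trial that describes itself as exploratory.

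Third, leaving out the start-of-period values is a legitimate choice. With equal correlations adjustment gains nothing, and the listed model terms are evidently not complete, since treatment itself is not named. A fuller analysis plan may settle the matter. A reader might infer that the plan wastes information or is mis-specified; that goes too far. What remains is that 69 days separate samples within a period against 98 between the end visits, so some gain is plausible at almost no cost.

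**Conclusion.** The inconsistency is real but lies between the abstract and the rest of the article. The 0.88 is sound for end-of-period concentrations and should not be carried over to change scores. Those would have 0.61 to 0.76 power under three of the four scenarios examined, and would match the end-value analysis only at a start-to-end correlation of about 0.895. That range rests on assumed correlations, with the end-to-end value held at 0.79.

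The unadjusted end-of-period analysis is valid. Baseline adjustment would move power from 0.887 to between 0.886 and 0.96, depending on the same unreported correlation. It is worth recommending as a cheap improvement and is not a correction of an error.

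**What to change.** 1. Define the primary variable once, as the serum concentration at the end of each treatment period, and align the abstract and Outcome measures with Statistical analysis. State that the 0.88 refers to this variable. This costs wording only.
2. Do not make raw change scores primary without a new power calculation that states the start-to-end correlation.
3. Add the start-of-period concentration to the mixed model as two terms: the participant's mean of the two start values, and each period's deviation from that mean. The deviation term does the work for the within-person comparison and costs one degree of freedom there, about 0.001 of power at worst.
4. Report the unadjusted model as a sensitivity analysis. Any carryover still present at visit 4 would be partly absorbed by the covariate, and the comparison of the two models would help to show it. The unadjusted model also matters because the protocol's missing-data rule drops participants who lack any variable an analysis needs, so a lost start-of-period sample would remove that person from the adjusted model.
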